### Sample size calculations

For the purpose of sample size estimation, the primary outcome of this study was difference in BMI Z-score at 12 weeks. Our own pilot data, and data from the largest RCT in obese adolescents yet published (209 children aged 8-16 with BMI > 95^th^ percentile; Savoye 2007) suggest the standard deviation in BMI Z-score in a non-passive weight loss intervention will be approximately 0.27. Assuming a 2-sided 0.05 significance level, a sample size of 52 participants per group would provide 80 % power to detect a clinically important treatment difference of 0.15 BMI Z-score. To account for a 25 % drop-out, we plan to enrol 70 participants in each group.

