### Recruitment and randomisation

The study will be advertised within the weight management centres in Victoria, Western Australia, New South Wales and the Australian Capital Territory as well as on the company website. Potentially eligible clients will be assessed in the weight management centres by consultants, guided by dietitians and/or a general practitioner for study eligibility. If participants who meet eligibility criteria are interested in participating in the study, they will be shown an information DVD. All participants will provide written consent that will be obtained by consultants in the weight loss centres from both the adolescent and their parent or guardian. Consenting adolescents will then be recruited into the study via telephone by a researcher.

Allocation to treatment group (intervention or wait-listed control) will occur using computer-generated random numbers. Group allocation will occur off-site by a statistician with no day-to-day study involvement in the trial. Individuals will be allocated 1:1 to the intervention group or wait-listed. Randomisation of the study participants will be stratified by the weight-management centre from which they are enrolled. Within each centre, randomisation will occur in blocks of either 6 or 8. Block size will be randomly selected and unknown to anyone except the study statistician ([name]). Treatment allocation will be stored in an online database, accessible only by the study statistician, and will remain unknown until revealed to the study co-ordinator on the day each participant is allocated to a treatment group. Due to the nature of the intervention masking participants to group allocation is not possible.

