### Outcomes

#### Anthropometry

All participants will have their baseline weight, height, waist, and body composition (using bioelectric impedance analysis (BIA); BODYSTAT Quad Scan 4000, BODYSTAT Ltd., Douglas, Isle of Man, UK) measured by trained Jenny Craig consulting staff using standard operating procedures. BMI Z-score will be calculated by the lambda-mu-sigma (LMS) method using Centre for Disease Control reference data (http://www.cdc.gov/growthcharts/percentile_data_files.htm) which takes into account age and gender. Participants will be required to self-assess their pubertal status using the Tanner stages of puberty scale [23, 24]. The intervention group will have weekly weight measurements, height measured every 4 weeks and waist and body composition assessed by BIA measured at 0 and 12 weeks. Wait-listed control participants will have all measurements taken at 0 and 12 weeks only.

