The initial approach to all analyses will be based on the ‘intention to-treat’ (ITT) principle, where all evaluable data is analysed in the treatment group according to which the participant was allocated. Additionally, because of the potential for differential between-group attrition due to the nature of recruitment, all analyses will be investigated to see whether results are sensitive to possible between-group imbalances in key demographic, social, or clinical characteristics. Characteristics of participants for whom follow-up data is available will be compared between groups, and variables significantly different at P < 0.05 will be identified. Multivariable regression models will be run with treatment group as the main effect and covariables including the value of the outcome at baseline and characteristics identified as differing between treatment groups at follow-up. All sensitivity analyses will be clearly labelled., Statistical significance will be defined as alpha = 0.05. All tests conducted will be two-tailed.

Outcomes measured at six months will be analysed using mixed-effects regression models with a random intercept for each participant. For continuous outcomes Gaussian family and identity link function, for binary outcomes a binomial family and logit link function, and for count outcomes a Poisson family and log link function will be used. All models will include time period (baseline/12 weeks/36 weeks) as a main effect, and other covariables will be included as appropriate.

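### The only stated check on differential attrition adjusts participants with week-12 data for characteristics that differ at P < 0.05, which cannot reveal dropout related to weight response

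*Protocol article*

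**What the plan says.** The Sample size calculations section allows for substantial loss: "To account for a 25 % drop-out, we plan to enrol 70 participants in each group". The Statistical analysis plan section analyses participants with evaluable data in the arm to which they were allocated. The 12-week primary model is a linear regression on treatment with adjustment for the baseline value of the outcome.

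The same section then announces a sensitivity investigation, "because of the potential for differential between-group attrition due to the nature of recruitment". The procedure is written out: "Characteristics of participants for whom follow-up data is available will be compared between groups, and variables significantly different at P < 0.05" are identified and entered, with the baseline outcome, in a further regression. These analyses are to be labelled as sensitivity analyses.

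The mixed-effects models in that section are for six-month outcomes. The Follow-up section collects those in the intervention arm only, so they give no randomised comparison at 12 weeks.

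On available data, the Anthropometry section states: "The intervention group will have weekly weight measurements, height measured every 4 weeks". Waist is measured at 0 and 12 weeks only, and controls have every measurement at 0 and 12 weeks only.

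**The concern.** The plan names a threat and then specifies a check that is poorly suited to it, for two reasons.

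- **How covariates are chosen.** Whether a characteristic reaches P < 0.05 depends on the number of participants left and the size of the imbalance, not on how strongly the characteristic predicts BMI Z-score or waist-to-height ratio. Moderate imbalances in strong predictors can be missed, and irrelevant characteristics can enter.
- **What the check can see.** It compares measured characteristics among participants with week-12 data. If adolescents are lost because of how their weight is changing, beyond what those characteristics explain, the adjusted and unadjusted estimates share the same bias and will agree.

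The document describes exits that could plausibly track weight change. Intervention participants may leave the program freely (Intervention: the JenMe program). Wait-listed participants who start the program early leave the study (Ethics and dissemination). Participants cannot be masked. Agreement between the two regressions could then be read as evidence that attrition did no harm, when the check had little ability to show otherwise.

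**Working it through.** **1. The plan's own figures.** Inputs from Sample size calculations: difference 0.15, SD 0.27, two-sided 0.05, 80% power, 25% dropout; 1:1 allocation from Recruitment and randomisation.

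- Normal approximation: n = 2 × (1.960 + 0.842)² × 0.27² / 0.15² = 50.9, so 51 per arm.
- Two-sample t-test: 51.84, so 52 per arm (power 80.1%).
- Inflation: 52 / 0.75 = 69.3, so 70 per arm.

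The stated 52 and 70 reproduce, so 52 per arm is used below as the number with week-12 data.

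**2. Chance of flagging a real imbalance.** Two-sample t-test, 52 per arm, 102 degrees of freedom, noncentrality = d × √(52/2) = 5.099 × d.

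| True imbalance d (SD) | Noncentrality | P(flagged at P < 0.05) |
|---|---|---|
| 0.2 | 1.02 | 17% |
| 0.3 | 1.53 | 33% |
| 0.4 | 2.04 | 52% |
| 0.5 | 2.55 | 71% |

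**3. Chance of flagging noise.** With k independent characteristics unrelated to dropout, P(at least one flag) = 1 − 0.95^k. The document does not give k; 5 to 20 is assumed.

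| k | P(at least one false flag) |
|---|---|
| 5 | 23% |
| 10 | 40% |
| 15 | 54% |
| 20 | 64% |

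**4. Outcome-related dropout.** Simulation with 70 per arm, SD of change 0.27, true effect zero, 10 characteristics unrelated to outcome or dropout, and 4,000 runs per scenario. In the outcome-related scenarios, the log-odds of dropout in the intervention arm rise with each SD of worse outcome. The mechanism and the arm-specific rates are assumptions; the document gives only 25%.

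| Nominal dropout (intervention/control) | Log-odds per SD | Bias, baseline-adjusted | Bias with P < 0.05 covariates | Type I error, without/with |
|---|---|---|---|---|
| 25%/25% | random dropout | 0.000 | 0.000 | 4.6%/4.5% |
| 25%/25% | 0.5 | -0.033 | -0.033 | 10%/10% |
| 25%/25% | 1.0 | -0.064 | -0.064 | 23%/22% |
| 35%/15% | 0.5 | -0.046 | -0.045 | 14%/13% |
| 35%/15% | 1.0 | -0.085 | -0.085 | 35%/35% |
| 35%/15% | 1.5 | -0.113 | -0.113 | 58%/57% |

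Against the target difference of 0.15, the bias runs from 0.033/0.15 = 22% to 0.113/0.15 = 75%. Adding the selected covariates changes the estimate by no more than 0.001. The simulated characteristics carry no information about outcome or dropout, so this shows what the rule cannot do when measured characteristics do not explain the loss. It does not show that adjustment never helps.

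**The case against.** The strongest case on the other side has five parts.

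- **The rule touches only a labelled sensitivity analysis.** This stands. A reader might infer that the primary result depends on data-driven covariate selection; it does not, because the primary model is fixed as treatment plus baseline outcome.
- **Chance selection is harmless in itself.** This also stands. With random dropout both models kept type I error near 4.5%. A reader might take the 23% to 64% false-flag figures as inflated error or bias, but they show only that the chosen covariates may be irrelevant. Differential attrition can also create real imbalances, and adjustment helps where loss depends only on baseline outcome and the selected characteristics.
- **The article is condensed.** A fuller plan may include imputation or use the interim weights, and nothing in the article rules that out. So it cannot be said that the trial has no other provision for missing data. What survives is that the threshold, the participants tested and the resulting model are all stated here, and they are a poor choice whatever else is added.
- **Leaving the program is not the same as missing data.** Correct. Someone who stops the program but is measured at week 12 has evaluable data and is included. The concern is confined to those without a week-12 value.
- **Control-arm loss may act in the other direction.** Correct. The simulated bias favours the intervention because only its arm was given outcome-related dropout. Exits of controls who start the program early could push the estimate either way.

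**Conclusion.** The point holds in limited form and should be addressed. For the 12-week outcomes the stated attrition check chooses covariates by a significance test that detects a 0.3 SD imbalance one time in three. It cannot expose bias from loss related to weight response. The harm is false reassurance about the primary result, not a defect in the primary model or the sample size.

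The detection rates assume 52 per arm with week-12 data. The false-flag rates assume 5 to 20 independent characteristics. The bias of -0.03 to -0.11 BMI Z-score, with type I error of about 10% to 58%, rests wholly on assumed dropout mechanisms and arm-specific rates. It illustrates scale and does not forecast this trial.

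A reader might also infer that the effect would be overstated by a fixed fraction, such as 1/0.75 − 1 = 33% at 25% dropout. The documents do not support that. It requires every lost intervention participant to have had no benefit, and it would apply to any trial under that assumption.

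**What to change.** 1. Replace the P < 0.05 rule with prognostic covariates fixed in advance and used regardless of significance: baseline outcome, age, sex, Tanner stage, centre (the stratification factor) and a socioeconomic item if the demographic questionnaire collects one.
2. Report the number without week-12 data, with reasons, by arm. Keep stopping the program apart from leaving the study.
3. Add a missing-data sensitivity analysis of all 140 randomised participants for both primary outcomes:
   - multiple imputation by arm, using interim weights and heights where they exist. That means the intervention arm and BMI Z-score only: controls have no interim measurements and waist has none in either arm;
   - delta-adjusted scenarios in both arms, including controls who leave by starting the program early, whom a reference-based analysis of the intervention arm alone would not cover;
   - reference-based imputation from the wait-list distribution for intervention participants without week-12 data.

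The cost is some wording and analysis work, wider intervals and a possibly less favourable sensitivity estimate. The primary model and the 70 per arm stay as they are, and no new data are needed.

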### Follow-up

All outcome measures will be assessed in the intervention participants at a follow-up at 36 weeks after commencement in the program (6 months after program completion), in order to track longer-term weight management. It will not be possible to follow-up the wait-listed participants as a control group as they will have the option to commence the program at end of their 12-week wait-listed period.

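### For continuous outcomes, the 36-week random-intercept model assumes equal correlation across unequally spaced visits; if correlation decays, the baseline-to-36-week interval is too narrow

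*Protocol article*

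**What the plan says.** The Statistical analysis plan section of the protocol article sets the longer-term model: six-month outcomes are to be analysed with "mixed-effects regression models with a random intercept for each participant". It gives the error families and links ("For continuous outcomes Gaussian family and identity link function, for binary outcomes a binomial family and logit link function", with a Poisson model for counts) and the time terms: "All models will include time period (baseline/12 weeks/36 weeks) as a main effect, and other covariables will be included as appropriate". It names no random slope, residual correlation structure or robust standard error.

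The Follow-up section restricts the 36-week data to one arm: "All outcome measures will be assessed in the intervention participants at a follow-up at 36 weeks after commencement in the program". It explains why: "It will not be possible to follow-up the wait-listed participants as a control group". The stated purpose is "in order to track longer-term weight management".

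The primary outcomes use a different model, a linear regression at 12 weeks adjusted for the baseline value.

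**The concern.** With a Gaussian outcome and categorical time, a random intercept alone is compound symmetry: the same variance at every visit, and the same correlation for weeks 0 and 12, weeks 12 and 36, and weeks 0 and 36. The design makes that doubtful. The gaps are 12 and 24 weeks. The first covers a program of weekly consultations, and the second covers optional support that some participants will use and others will not. The Background also reports that in an earlier Australian program the loss levelled off and then partly reversed. Correlation that weakens over time, or courses that fan out, would be unsurprising.

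If that happens, the model pools three different change variances into one and misstates the precision of the longest change. It also predicts a missing 36-week value equally from baseline and week 12, when week 12 would be the better guide. With no control arm at 36 weeks, the within-arm change and its interval are the trial's whole evidence on longer-term weight.

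**Working it through.** **Inputs from the article.** Visits at 0, 12 and 36 weeks; up to 70 intervention participants; 25% drop-out allowed for; two-sided alpha 0.05. The article states no figure for the 36-week analysis. Its 12-week sample size reproduces: a t-test with 52 per group, SD 0.27 and difference 0.15 has power 0.801, and 52/0.75 = 69.3, rounded up to 70. That figure does not bear on this point.

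**Assumed inputs.** The article gives no correlations between visits, so two decaying sets are assumed, with equal variances:
- Set A: 0.90 (0-12), 0.85 (12-36), 0.75 (0-36).
- Set B: 0.92 (0-12), 0.88 (12-36), 0.82 (0-36).

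**Formula, complete data.** The true variance of a change is proportional to 1 - r for that pair. The random-intercept model gives every change the mean of the three. So model SE / true SE = sqrt(mean(1 - r) / (1 - r of the pair)), and 95% interval coverage = 2Φ(1.96 × ratio) - 1.

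- Set A: mean(1 - r) = (0.10 + 0.15 + 0.25)/3 = 0.1667.
- Set B: mean(1 - r) = (0.08 + 0.12 + 0.18)/3 = 0.1267.

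| Change | Set A ratio | Set A coverage | Set B ratio | Set B coverage |
|---|---|---|---|---|
| 0 to 36 | sqrt(0.1667/0.25) = 0.816 | 89% | sqrt(0.1267/0.18) = 0.839 | 90% |
| 0 to 12 | sqrt(0.1667/0.10) = 1.29 | 99% | sqrt(0.1267/0.08) = 1.26 | 99% |
| 12 to 36 | sqrt(0.1667/0.15) = 1.05 | 96% | sqrt(0.1267/0.12) = 1.03 | 96% |

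**Other patterns, 0-to-36 change.**
- Correlation decaying steadily, from 0.95 to 0.5 at a 12-week lag: ratio 0.82 to 0.90, coverage 89 to 92%.
- Individual slopes fanning out (slope SD 0.05 to 0.27 per 36 weeks, residual SD 0.05 to 0.10): ratio 0.74 to 0.97, coverage 85 to 94%.
- Equal correlations: ratio 1.00, coverage 95%.
- Correlations 0.90 (0-12), 0.85 (0-36), 0.80 (12-36): ratio 1.00.
- Correlations 0.85 (0-12), 0.90 (0-36), 0.85 (12-36): ratio 1.15, so the interval is too wide.

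**Drop-out, by simulation.** Settings: 70 participants, REML, 500 runs, SD 0.40 (assumed), true 0-to-36 change -0.10, normal critical values, about 22 to 25% missing at week 36. Decay means correlation 0.9 at a 12-week lag.

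| Truth and drop-out | Analysis | Bias | Model SE / empirical SE | Coverage |
|---|---|---|---|---|
| Decay, at random | Random intercept | -0.003 | 0.031 / 0.039 | 87% |
| | Unstructured | -0.002 | 0.038 / 0.039 | 93% |
| Decay, depends on 12-week change | Random intercept | -0.013 | 0.031 / 0.041 | 85% |
| | Unstructured | +0.003 | 0.039 / 0.042 | 93% |
| | Complete cases | -0.032 | 0.040 / 0.042 | 86% |
| Equal correlation 0.9, depends on 12-week change | Random intercept | +0.001 | 0.024 / 0.025 | 94% |
| | Complete cases | -0.019 | 0.024 / 0.026 | 84% |

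A second simulation (1,500 runs, Sets A and B, equal or growing SDs, about 25% missing dependent on the 12-week change) gave random-intercept bias of -0.013 to -0.022 and coverage of 83 to 87%. The unstructured bias was within 0.001.

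The bias scales with the assumed SD. If the article's 0.27 were the SD at each visit, -0.013 would become -0.013 × 0.27/0.40 = -0.009.

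**The case against.** The strongest reply is that the harm is conditional. A reader might infer that the 36-week intervals will come out too narrow. The documents do not support that: they give no correlations, equal correlation produces no error, and some patterns make the interval too wide. This stands, and the point must be put as a conditional.

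A reader might also infer that the maintenance result itself is anti-conservative. Maintenance read most directly is the change from week 12 to week 36. Under steady decay or Sets A and B that SE is about right (ratio 0.97 to 1.05), and the baseline-to-12-week SE errs on the wide side. Only the baseline-to-36-week change is affected in the flattering direction. This stands too.

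A third tempting reading is that drop-out is handled badly. It does not follow. A likelihood-based mixed model uses every available visit and is valid under missing at random when its covariance fits. Even with the wrong covariance it cut the complete-case bias from -0.032 to -0.013. Larger biases need more loss than planned: at about 38% missing with stronger dependence, the random-intercept bias was -0.025 to -0.042, but the article allows for 25%. Nor is all of the shortfall from 95% due to the random intercept, since the unstructured model reached only 93% with normal critical values.

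Finally, a condensed article may leave covariance detail to a fuller plan, and this one does not rule out additions. That carries less weight. The article does not leave the dependence open; it names the random intercept as the model. The proposal replaces a stated choice with a better one.

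**Conclusion.** The point holds as a conditional one, for continuous outcomes only. The stated model fixes one variance and one correlation across unequally spaced visits that span two different phases of support. If correlation decays as assumed in Sets A and B, the baseline-to-36-week SE is 16 to 18% too small and the nominal 95% interval covers 89 to 90% with complete data. With about 25% missing dependent on the 12-week change, there is a modest bias of about -0.01 to -0.02 BMI Z-score towards overstating maintained loss, and coverage of 83 to 87%. All of these sizes rest on assumed correlations and SDs.

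For the logit and log-link models the equal-correlation assumption applies on the linear-predictor scale, so these figures do not carry over. A reader might also suppose that the main trial result is at risk. It is not: the primary 12-week comparison uses baseline-adjusted linear regression and does not involve this model. This is a worthwhile correction to a secondary, single-arm follow-up.

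**What to change.** For continuous 36-week outcomes, state a repeated-measures mixed model in the intervention group with time (baseline, 12 weeks, 36 weeks) as a categorical effect and an unstructured 3x3 covariance, fitted by REML with Kenward-Roger degrees of freedom. Name the two contrasts to be reported: 36 weeks against baseline and 36 weeks against 12 weeks. If the model does not converge in the small blood or DXA subsets, fall back on participant-level robust standard errors. Robust errors correct the interval but do not remove drop-out bias.

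The change takes a sentence or two. It adds four covariance parameters (six instead of two), which up to 70 participants at three visits can support, and may widen the 36-week interval slightly. If the correlations are in fact equal, little is lost: with random drop-out and equal correlation of 0.9, both models had a mean SE of 0.0235.

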### Ethics and dissemination

It has previously been demonstrated that children randomised to wait-listed or only given written information (control groups) gain weight [35]. Allocating overweight and obese children to be wait-listed for 12 weeks raises ethical concern as weight gain in children that are not treated could be disadvantaged, particularly with children that have identified their need for weight-loss assistance in a community setting. In the current study, as participants will not have weight-related co-morbidities, ethical permission has been approved to delay treatment in a wait-listed control group for 12 weeks after which they will have the opportunity to undertake the commercially available weight management program. Participants have the right to withdraw from the study at any time, for any reason. If a wait-listed control participant chooses to commence the program immediately, it will be made available to them, but they will not participate in the study. Ethical approval for the study has been granted by Monash University Human Research Ethics Committee (approval no: CF11/3687–2011001940).

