## Methods

### Study design and participants

The current study is a multicentre, parallel-group randomised controlled trial. Adolescent boys and girls aged 13 to 17 years who apply to join the commercial weight management program will be screened for eligibility to participate. Individuals who do not meet the health screen requirement, a standard practice for enrolment to Jenny Craig weight management programs, will not be eligible for inclusion in the study. Exclusion criteria of the program include being aged less than 13 years or greater than 17 years; having diagnosed diabetes; being pregnant; having given birth to a child during adolescence; having a medical condition or using medications related to weight co-morbidities (except asthma). Individuals who have a BMI Z-score of ≥ 1.282, indicating that they are above the 85^th^ percentile for BMI for their age and gender, will be invited to participate in the study. Participants will be randomised into either the treatment group or the wait-listed control group. The treatment group will enter the weight management program immediately, and the control group will be wait-listed for 12 weeks. Figure 1 shows the study flow. Behavioural questionnaires and diaries will be completed during the week prior to the first consultation where anthropometric characteristics of participants will be recorded. The same questionnaires and diaries will be repeated during week 12 (the final week of the program for participants in the interventions group), and participants will again have anthropometric characteristics recorded at the end of week 12. Primary outcome measures will include changes in BMI Z-score and waist to height ratio. Secondary outcome measures will include changes in physical activity levels, behaviour and psychosocial wellbeing. Participants will have the option to volunteer to have further cardio-metabolic risk factors and body composition examined. All experimental procedures are being conducted in accordance with the Declaration of Helsinki and were formally approved by the Monash University Human Research Ethics Committee (CF11/3687–2011001940).

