**Independent menu planning**			
Getting started on your own	1. Your own menu guide	2. Working out grocery serves of recipes	3. Working out grocery serves of packaged foods from labels

Initially the participant will follow the menu that includes pre-packaged food provided by the commercial program, combined with their own grocery items. Throughout the program the adolescent, with the support of their consultant and parent or guardian will learn how to plan their own menus using all of their own foods, and either during or following the 12 week program, they will eventually transition onto their own menu planning (Table 1). In accordance with usual practice at Jenny Craig, once the 12 week ‘JenMe’ program is complete, adolescents have the option to receive ongoing, individually-tailored support, depending on the need for further weight-loss or weight-maintenance up to the age of 18 years of age as part of their Jenny Craig membership. Also, as with any commercial program, participants are free to withdraw from the program at any stage, for any reason.

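### Wait-listed participants who start the program early leave the study after randomisation, which defeats the intention-to-treat principle and can bias both primary comparisons in an unknown direction

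*Protocol article*

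**What the plan says.** All references are to the protocol article.

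- **Study design and participants:** "Participants will be randomised into either the treatment group or the wait-listed control group". Under Recruitment and randomisation, consent precedes allocation. Being wait-listed is therefore a result of randomisation.
- **Ethics and dissemination:** "If a wait-listed control participant chooses to commence the program immediately, it will be made available to them, but they will not participate"; the sentence refers to taking part in the trial. The general right to leave is stated separately, just before: "Participants have the right to withdraw from the study at any time, for any reason".
- **Intervention: the JenMe program** (text after Table 1): "participants are free to withdraw from the program at any stage, for any reason". Nothing there says that leaving the program ends study participation.
- **Statistical analysis plan:** analyses follow intention to treat, "where all evaluable data is analysed in the treatment group according to which the participant was allocated". Sensitivity analyses are planned "because of the potential for differential between-group attrition due to the nature of recruitment". For these, "Characteristics of participants for whom follow-up data is available will be compared between groups", and variables that differ at P < 0.05 are added as covariables.
- **Anthropometry:** wait-listed controls have all measurements at 0 and 12 weeks. The intervention group has weekly weights, height every 4 weeks, and waist at 0 and 12 weeks.

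**The concern.** The early-start rule removes randomised people from one arm because of how they respond to their allocation. An intervention participant who stops the program has changed treatment but is not said to leave the study. A control who starts the program has also changed treatment, yet does leave it. Only the control arm is thinned in this way, and the trait that drives it, eagerness to begin treatment, is plausibly related to weight change over 12 weeks.

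Early starting is foreseeable. Participants are adolescents who applied to join this very program, and the ethics text itself worries about delaying young people who have recognised that they need help.

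At stake are both primary outcomes, BMI Z-score and waist-to-height ratio at 12 weeks. If the leavers would have done better than average while waiting, the remaining controls look worse and the program looks more effective than it is. If the leavers would have gained more, the effect is understated. Week-12 measurements that are never taken cannot be recovered at analysis.

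**Working it through.** **1. The plan's own figures reproduce.** From Sample size calculations: difference 0.15, SD 0.27, two-sided alpha 0.05, power 80%, drop-out 25%. The two-sample t-test needs n = 51.84, so 52 per group (power 0.801). Enrolment is 52 / (1 − 0.25) = 69.3, so 70 per group. Conversely, 70 × 0.75 = 52.5 evaluable per arm, with power 0.805. No stated number is wrong; the problem lies in who is followed and analysed.

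**2. The rules side by side.** Randomisation creates the wait-list, and the early-start rule acts on people already on it, so the exclusion comes after randomisation. The intention-to-treat sentence keeps people in their allocated group but covers evaluable data only. An early starter who is no longer followed has no week-12 value, so both sentences can be applied literally. In that case, however, it is the protocol's own rule that makes the data non-evaluable. This is a designed and avoidable loss, and the intention-to-treat label does not reveal it.

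**3. Possible bias.** Let q be the share of controls who leave and g the difference in untreated 12-week BMI Z-score, adjusted for baseline, between leavers and stayers. Removing the leavers shifts the control mean by −q × g. The article gives neither q nor g, so the values below are assumptions.

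| q | abs(g) | Shift in control mean (either direction) | Share of 0.15 |
|---|---|---|---|
| 10% | 0.05 | 0.005 | 3% |
| 10% | 0.15 | 0.015 | 10% |
| 20% | 0.05 | 0.010 | 7% |
| 20% | 0.15 | 0.030 | 20% |

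The adjusted difference is the relevant one because the primary model includes the baseline outcome as a covariable. The top value of g equals the whole target effect.

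**4. Loss of controls.** If early starters come on top of the 25% drop-out, 20% fewer evaluable controls (52.5 × 0.80 = 42) lowers t-test power from 0.805 to 0.757. If they fall within the 25%, power is protected but comparability is not.

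**5. Cost of keeping early starters.** Suppose 15% of evaluable controls start early and each gains the full effect. The contrast becomes 0.15 × (1 − 0.15) = 0.1275. With SD 0.27 and 52.5 per arm, power is 0.67. Removing that 15% instead (52.5 × 0.85 = 44.6 controls, contrast assumed to stay at 0.15) would give 0.77.

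**The case against.** **There is no contradiction.** A reader might infer that the two sections cannot both hold. The text does not support that, because the evaluable-data qualifier lets them coexist. This part of the objection stands. What remains is a conflict with the principle invoked, brought about by a rule that creates informative missing data.

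**The rule may cover only those who refuse the wait at once.** It speaks of starting immediately and follows directly on the right to withdraw. This narrower reading is fair and may reduce the numbers. It does not move the exclusion to before randomisation, since even someone who declines on the day of allocation has been allocated. Starting the program is also not the same as refusing measurement.

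**The protocol already deals with attrition.** It foresees differential attrition, plans labelled sensitivity models and allows for 25% drop-out. That deserves credit, but the models use only observed characteristics that happen to differ at P < 0.05 among those followed up. With about 52 per arm, a non-significant difference does not show balance, and motivation to start early is not recovered by such adjustment. The drop-out allowance protects numbers only.

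**The bias could be made to look larger.** Setting the gap at one planning SD gives 0.20 × 0.27 = 0.054, or 36% of the target. That ignores baseline adjustment and supposes a gap 1.8 times the whole target effect (0.27 / 0.15). It is not supported.

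**Retaining early starters costs power.** This stands: in the worst case the loss exceeds that from excluding them. But the power under exclusion relates to a comparison that may be biased, so it is no reason to drop randomised participants.

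**Conclusion.** The concern holds in this form: the early-start rule is a one-arm, post-randomisation exclusion linked to motivation. It defeats the intention-to-treat principle and can bias both primary comparisons. The planned sensitivity models cannot remove that bias.

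Size and direction are unknown. On the assumed ranges (10–20% leaving, adjusted gap 0.05–0.15), the control mean for BMI Z-score shifts by 0.005–0.03, about 3–20% of the 0.15 target. No comparable figure can be given for waist-to-height ratio, for which the article states no target or SD.

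A reader might infer that the rule is known to flatter the program. The article supports no such direction: eager leavers and leavers who are gaining weight would push the estimate opposite ways.

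**What to change.** Leave access to the program unchanged, and reconcile Ethics and dissemination with the Statistical analysis plan along these lines:

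- A wait-listed participant who starts the program early stays in the study unless consent for measurement is withdrawn.
- That participant attends the week-12 control assessment already described under Anthropometry (weight, height and waist), timed from the start of the wait-list period, and is analysed in the wait-list arm.
- The number and timing of early starts are reported.
- A labelled sensitivity analysis sets measurements after an early start to missing and multiply imputes them.

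Routine program measurements should not be relied on instead. The article describes weekly weights and 4-weekly heights for the intervention group only, and waist is taken only at weeks 0 and 12, so they would not secure the second primary outcome.

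The cost is a short change of wording and some effort to bring early starters back at week 12; that assessment is already planned for controls. The protocol should also state the dilution openly: in the worst case worked above, about 0.13 instead of 0.15, with power about 0.67 at 52.5 evaluable per arm.
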